## Introduction

### Background and rationale

Despite the remarkable technological progress of modern medicine, communication between patients and doctors is still an issue today. Trying to guarantee a concise, complete and transparent communication of information, possibly appropriate to the educational level of the patient, remains nowadays as in the past, a complex challenge for the clinician.

In the context of Emergency Departments (EDs), this challenge is made even more difficult due to the presence of various factors: overcrowding, simultaneous management of multiple patients, lack of privacy, noise, interruptions, and time constraints [].

Additional patient-specific elements can further complicate patient-provider communication: cultural differences, language barriers, differences in educational levels and demographics, etc. [].

Furthermore, both medical school and higher specialty training in Emergency Medicine currently dedicate little time to the development of communication skills: however, these techniques can be learned by doctors along with technical skills, which are usually prioritized in the educational curricula of trainees [5] [1,6].

A task force of the 'Society for Academic Emergency Medicine' has identified five essential elements in patient-provider communication in the Emergency Department: establishing rapport, providing information, providing comfort, creating a collaborative relationship and gather information [7].

Current literature on this subject shows that doctors' explanations at discharge are often deficient in one or more of the aforementioned areas [8,9]. In one study, the average duration of doctors' explanation of discharge instruction was 76 seconds, due to overcrowding and time constraints [8].

Other studies have shown that ED-patients' comprehension often shows deficiencies across several domains, such as diagnosis and its causes, ED care, post-ED care, return instructions, etc.[10-11].

Comprehension is the major predictor of compliance with discharge instructions [12], and compliance with discharge instructions has been associated with better patient outcomes [13,14].

All this evidence highlights the need for effective interventions aimed at improving communication in emergency departments.

A 2012 review on the topic summarizes some of the various solutions described in the current literature such as the standardization of discharge instructions in a diagnose-specific manner and the simplification of their language content [15].

Graphic illustrations or “comics” have showed benefits in the comprehension of patients in a variety of settings, including the discharge from ED [16,17]. Similarly, the use of video clips has been investigated in few studies, both in adult and pediatric EDs, showing promising results [18,19,20,21].

## Objectives

The aim of this study is to assess the utility of two interventional videos, shown to patients discharged from the ED with a diagnosis of atrial fibrillation or deep vein thrombosis. We have focused our attention on these two medical conditions because they share some important features: they are frequently seen in EDs; their main complication (stroke and pulmonary embolism) can cause significant morbidity and mortality; both conditions and their related complications are probably not

very intuitive to comprehend for the general population. In fact, the understanding of these conditions implies the knowledge of a number of pathological processes, with which most people are unfamiliar.

The primary hypothesis is that patients enrolled in the study group will show a higher degree of comprehension of their medical condition and its related complications, as compared to the control group. Secondly, we will also analyze any possible effect of the videos on the knowledge of the therapy prescribed, return instructions and patients' satisfaction with the quality of communication in the ED.

Eventually, we will examine the association of some factors with the outcomes (age, sex, level of education, atrial fibrillation vs. deep vein thrombosis group).

## **Trial design**

We designed a multicentric, pragmatic, parallel groups trial, with 1:1 randomization, that involves patients discharged from two Emergency Units with a diagnosis of atrial fibrillation (AF) or deep vein thrombosis (DVT).

The study aims to demonstrate the superiority of the intervention, assessed with a telephone interview that is conducted within 48 hours from patient's discharge. This protocol was developed following the SPIRIT checklist.

## **Methods: Participants, interventions, and outcomes**

### **Study setting**

The trial takes place two Emergency Units, namely the “*S.C. Pronto Soccorso Accettazione of the IRCCS Fondazione Policlinico San Matteo*” (Pavia, Italy) which includes the Emergency Department and its adjacent Short-Stay Unit, and the Emergency Unit 2° *Medicina Generale, ASST Spedali Civili di Brescia* (Brescia, Italy).

Both institutions are tertiary referral hospitals, serving as “Hub” centres for STEMI, Stroke and Trauma patients.

## Eligibility criteria

Inclusion criteria are the following:

- Age >18
- Being diagnosed with one of the two medical conditions under study: patients with first-time diagnosis of deep vein thrombosis; patients with first-time diagnosis of atrial fibrillation; patients with second episode in life of atrial fibrillation who have never been prescribed take-home medications for its cure or prevention of recurrence (anticoagulants, antiarrhythmic drugs including beta-blockers)
- Being discharged home directly from the Emergency Department/Emergency Unit
- Capacity of the patient to understand the explanations and instructions provided by the doctor (this includes excellent command of the Italian language)
- Having provided a valid phone number
- Having signed the informed consent

In case of patients lacking capacity, and in all cases of patients judged by the recruiting doctor as incapable to safely receive the discharge instructions, the caregiver will be enrolled to the study with identical modalities.

In the context of a pragmatic trial, we did not set exclusion criteria in terms of education level and comorbidities of the enrolled patients.

Exclusion criteria:

- Previous diagnosis of deep vein thrombosis
- Two or more previous episodes of atrial fibrillation; or one previous episode of atrial fibrillation for which the patient has been prescribed one of the following take-home medications: anticoagulants, antiarrhythmic drugs including beta-blockers.
- Being hospitalized

## Interventions

### *Study group*

All subjects enrolled in the study group are shown during the discharge process the video related to the patient's condition (DVT vs AF), using it as a graphic support to the doctor's verbal explanation of the diagnosed pathology and its potential main complication.

For the purposes of the study we have selected two video clips, available on various internet sites and not covered by any copyright restrictions; these have been modified and shortened to make them suitable to use in our study setting.

The clips last between 27 and 45 seconds and show the pathophysiological process underlying the two diseases under study, namely deep vein thrombosis and atrial fibrillation.

The SIs show the videos to patients on the institutional computer or, alternatively, on their personal smartphone / tablet (in any case in resolutions from 480 pixels to 720 pixels). The content of these video clips is adequate for adults with all levels of education. In addition to that, videos are purposely without audio content, as it is specifically requested that SIs provide explanations and comments according to what is shown on the screen, guiding patients during the vision of the clip. In particular, SIs are asked to structure the explanation as follows: a) describe the relevant anatomical structures and the physiological processes in normal conditions (lower limb veins and venous circulation/heart chambers and normal blood flow between atria and ventricles); b) describe the pathological process that determines formation of a blood clot in the respective anatomical sites (stagnation of blood in proximity of venous valves with formation of a thrombus/ fibrillation of the right atrium, stagnation of blood and formation of a thrombus in the atrium); c) describe the dislocation of the thrombus to reach the target anatomical site (lung/brain); d) describe the complications derived from clot's dislocation to the target anatomical site (pulmonary embolism/stroke). Although doctors follow the steps described above, which are based on the structure of the videos, we did not aim to standardize the linguistic style of their explanations. As an example, they could use the term "thrombus" or "clot" or any other synonym they believe is suitable for the comprehension of the patient, even recurring to street slang or dialectal forms if deemed appropriate.

Doctors can pause and rewind the clip at their discretion or if the patient requests to do so.

All patients will receive standard written discharge instructions.

### **Control group**

Patients of the control group receive discharge explanations without the aid of any video or graphic support. Following a pragmatic approach, we have asked doctors to express themselves in the way

they are used to in their clinical practice, which is based on the doctor's verbal and non-verbal communication skills.

All patients will receive standard written discharge instructions.

### **Outcomes**

The main outcome will be patients' comprehension of the domains directly related to the video contents, i.e., knowledge of the *diagnosis* and its potential *complication*, corresponding to interview's questions 1-3-4 (see the attached file *Telephone Interview*).

Secondary outcomes will be the knowledge of the prescribed therapy and patients' satisfaction (see the attached file *Telephone Interview*).

The outcomes will be measured through a telephone interview, consisting of a set of questions specifically designed for the purposes of this study (see the attached file "*Telephone interview*"). The interview is made of six questions, focusing on the different domains of comprehension.

The telephone interview is conducted by one of the two researchers responsible for this task. Audio files are then stored on a computer and subsequently reexamined by both reviewers, who will assign a score to each question contained in the interview (see the attached file "*Telephone interview*").

We developed a scheme to aid the reviewers in the interpretation of patients' answers, to reduce reviewers' inter-operator variability (see the attached file *Interpretation of patients' answers*).

Patients' answers will receive a score on a 4-point Likert scale (ranging from zero to three) from low to high knowledge.

Scores from the two independent reviewers will be summed to obtain an overall score. The score for the main outcomes will therefore range: 0-18 for the main outcome (questions 1-3-4), 0-6 for the knowledge of the prescribed therapy (question 2), 0-12 for patient's satisfaction (questions 5-6).

To the best of our knowledge, no currently available validated questionnaires would serve for the purpose of our study, i.e., for the simultaneous measurement of different domains of comprehension across two different medical conditions.

Hence, we have developed the ad-hoc interview and its related interpretation scheme using face and content validity. Construct validation would require an amount of time and resources equivalent to that of the trial itself, pushing it beyond practical feasibility.

In this second version of the protocol, we added two safety outcomes. The first is patient adherence to anticoagulation prescribed at hospital discharge. The second outcome is incidence of the main complication (stroke/pulmonary embolism) at a median follow up. This amendment is felt necessary due to relatively frequent patient-reported non-adherence to anticoagulants observed during telephone interviews.

Data for adherence rate to anticoagulants will be obtained from an additional review of the audio recording of the interview. This will be performed by one of the two reviewers.

Incidence of complications at median follow up will be assessed via a second telephone contact with recruited participants (patients or caregiver), using the same contact information provided at the time of recruitment. We will make a maximum of five attempts of contact, after which participants will be considered lost at follow up.

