### Telephone Interview

- 1. Could you tell me the name of the medical condition you have been diagnosed with and explain what it is in your own words?**

☐ Insufficient ☐ Sufficient ☐ Good ☐ Excellent

- 2. Have you been prescribed new take-home medications in the Emergency Department for this medical condition?**

☐ Insufficient ☐ Sufficient ☐ Good ☐ Excellent

- 3a). (For those patients who have been prescribed new take-home medications) What are these drugs for and for how long should you take them? What are the possible complications of your medical condition?**

☐ Insufficient ☐ Sufficient ☐ Good ☐ Excellent

- 3b). (For patients who have not been prescribed new take-home medications) Do you know why you have not been prescribed new medications? When are you going to have a follow-up visit? What are the possible complications of your medical condition?**

☐ Insufficient ☐ Sufficient ☐ Good ☐ Excellent

- 4. What symptoms would worry you enough to return to the Emergency Department?**

☐ Insufficient ☐ Sufficient ☐ Good ☐ Excellent

- 5. While in the Emergency Department did you get a chance to ask your doctor questions on your medical condition?**

☐ No, none of them ☐ Only a few of them ☐ Nearly all I had in mind ☐ Yes, all of them

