| Good         | The patient knows two of the three criteria listed above (purpose of the medication/treatment duration/technical term of the main complication).                                                                   | 
Examples (AF) <<I have to inject heparin to make my blood thinner until I see a cardiologist, otherwise I could get worse>>
 
(DVT) <<I need to inject heparin to make my blood more fluid, in order to avoid a pulmonary embolism to
 |

|           |                                                                                                                                                      |                                                                                                                    |
|-----------|------------------------------------------------------------------------------------------------------------------------------------------------------|--------------------------------------------------------------------------------------------------------------------|
|           |                                                                                                                                                      | occur; I can't remember though for how long I should continue taking it>>.                                         |
| Very good | The patient shows knowledge in all the criteria listed above (purpose of the medication/treatment duration/technical term of the main complication). | Example (AF) <> |

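### The 0-18 primary score is labelled diagnosis and complication, but it also contains therapy, follow-up and return-symptom items that the Objectives treat as secondary or the video script does not cover

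*Protocol*

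**What the plan says.** The Protocol's Objectives section sets the primary hypothesis as a "higher degree of comprehension of their medical condition and its related complications" in the video group. It then lists, as a second tier, "any possible effect of the videos on the knowledge of the therapy prescribed, return instructions" and satisfaction.

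The Outcomes section calls the main outcome "comprehension of the domains directly related to the video contents", names those domains as diagnosis and complication, and maps them to questions 1, 3 and 4. Each answer is scored on a "4-point Likert scale (ranging from zero to three") and the two raters' scores are added, giving "0-18 for the main outcome (questions 1-3-4), 0-6 for the knowledge of the prescribed therapy (question 2"). Return instructions do not appear among the secondary outcomes there.

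The Telephone Interview and its scoring guide show what the items contain:

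- Question 1 asks for the name and an explanation of the condition.
- Question 3a asks "What are these drugs for and for how long should you take them", and then about complications. Its second-highest level reads "The patient knows two of the three criteria listed above (purpose of the medication/treatment duration/technical term of the main complication"). Question 3b, for patients given no new drug, uses the reason for no drug, the check-up date and the complication.
- Question 4 asks "What symptoms would worry you enough to return to the Emergency Department". It is scored by the share of a symptom list that the patient names (6 entries for DVT, 9 for AF). Both lists include iatrogenic bleeding.

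The Interventions section scripts the video commentary in four steps: normal anatomy and physiology, clot formation, dislocation, and the resulting embolism or stroke.

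**The concern.** The two sections disagree about what is primary. Return instructions are a secondary aim in the Objectives, yet they form a third of the primary score in Outcomes and then disappear as an outcome of their own. Therapy knowledge is secondary in both sections, yet two of the three criteria in question 3 concern therapy or follow-up. Treatment duration, check-up date and bleeding are not in the scripted commentary, so the statement that the domains relate directly to the video is not true of every item.

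What is at stake is the meaning of the primary result. A difference on the total could come from diagnosis and complication, from therapy and return items, or from a mixture, and the total alone cannot tell these apart. Conversely, if the video improves only what it shows, points that do not respond dilute the effect. This is a practical issue: Supplementary Data 5 already reports a between-arm difference of 2.65 points under a label that mentions only the condition and its main complication.

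**Working it through.** **Score range (Outcomes).** 3 questions × 3 points × 2 raters = 18. The stated range is reproduced, and each question carries 6 points.

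**Sample size (Sample size section).** Inputs: control score 10, effect 20% of 10 = 2 points, SD 4, two-sided alpha 5%, power 80%.
- Normal approximation: n = 2 × (1.96 + 0.84)² × 4² / 2² ≈ 63 per group.
- A t-test with 64 per group has power 80.1%. Taking the Mann-Whitney relative efficiency as 1 for a uniform distribution, 64 is reproduced.
- Loss of 10%: 64 / 0.90 = 71.1, rounded up to 72, as stated.

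**Composition of the 18 points.** In question 3 the levels above the lowest correspond to one, two or three criteria known. Each criterion is therefore worth one level per rater, or 2 points.

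| Content | Item | Points | Share |
|---|---|---|---|
| Diagnosis | Question 1 | 6 | 33.3% |
| Naming the complication | Question 3 | 2 | 11.1% |
| Drug purpose, or reason for no drug | Question 3 | 2 | 11.1% |
| Duration, or check-up date | Question 3 | 2 | 11.1% |
| Return symptoms | Question 4 | 6 | 33.3% |

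**Share outside diagnosis and complication, on three readings of question 4.**
- All of question 4 is complication recognition: 4/18 = 22%.
- Only symptoms readable as embolism or stroke count, pro rata. This is an assumption: 5 of 6 for DVT (all but bleeding) and 7 of 9 for AF (all but bleeding and palpitations). DVT: 6 × 5/6 = 5 points on target, so (10 − 5)/18 = 28%. AF: 6 × 7/9 = 4.67, so (10 − 4.67)/18 = 30%.
- The Objectives' own classification, with return instructions secondary: (4 + 6)/18 = 56%. The remaining 8/18 = 44% is diagnosis plus the named complication.

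**What a total can hide.** A patient with no credit in question 1 and none for naming the complication can still score 4 + 6 = 10, which equals the assumed control median. A patient who never names the complication can still score 6 + 4 + 6 = 16.

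**Illustrative dilution.** Assume the 2-point effect is spread evenly over the 18 points, only on-target points respond, and SD stays at 4. With 64 per group the standard error is 4 × √(2/64) = 0.707, and power ≈ Φ(difference/0.707 − 1.96).
- All 18 points respond: 2/0.707 = 2.83; power 81% by this approximation.
- Questions 1 and 4 and the complication criterion (14/18): difference 1.56; 1.56/0.707 = 2.20; power 59%.
- Question 1 and the complication criterion only (8/18): difference 0.89; 0.89/0.707 = 1.26; power 24%.

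**The case against.** The strongest defence is that question 4 largely measures the complication. The DVT list leaves out leg pain and swelling, and five of its six entries can be read as signs of pulmonary embolism. Seven of the nine AF entries can be read as signs of stroke. The top level needs 4 of 6 or 6 of 9 symptoms, so it can be reached without bleeding or palpitations. This stands. A reader might infer that most of the primary points are off target, but that holds only if the whole of question 4 is excluded.

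Drug purpose is also close to the video: scoring examples for question 3a link the blood thinner to avoiding embolism or stroke. If purpose counts too, only duration or check-up date is clearly outside, at 2/18 = 11%. That is fair on content, but the Objectives still class therapy knowledge as secondary, so the labels remain in conflict.

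A reader might also infer that therapy knowledge is counted twice. It is not: question 2 scores drug names and dosage, question 3a scores purpose and duration, and no item enters two outcomes.

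The 24% power figure is a worst case, not a finding that the trial is underpowered. The Sample size section states its 2-point effect for the actual 0-18 score. The even spread and the unchanged SD are assumptions made here for illustration.

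Finally, the primary outcome is fixed unambiguously by item and range, and the Protocol openly says that it rests on face and content validity. That is true, but it makes the content of the items matter more, because nothing else supports the label.

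**Conclusion.** The Objectives and Outcomes sections contradict each other, and the 0-18 total is a mixed measure of diagnosis, complication, therapy or follow-up, and return symptoms. The share outside the stated construct is 22% to 30% when question 4 is read wholly or mostly as complication recognition, and 56% by the Objectives' own classification. The choice among these depends on how question 4 is read, which the Protocol leaves inconsistent.

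It would be too strong to say that the primary hypothesis goes untested. Even the strictest count leaves 8 of 18 points directly on diagnosis and complication. The supportable conclusion is that a difference on the total, positive or null, cannot be attributed cleanly to those two domains. The illustrative power of 24% to 59% shows the direction and possible size of dilution under the stated assumptions only.

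**What to change.** 1. Keep the 0-18 total as the primary outcome, but describe it as overall discharge knowledge. Restate the primary hypothesis and the Objectives to match, and remove the claim that all its items relate directly to the video.
2. Report questions 1, 3 and 4 by arm as component analyses. Record the three criteria of question 3 separately from the stored recordings; the raters already have to judge them to assign a level.
3. Identify question 4 as the return-instructions outcome, so that this secondary aim has a measure again.
4. Present a narrower score (question 1 plus the complication criterion, range 0-8) only as a supporting analysis labelled post hoc. It should not replace the primary outcome: arm-level results for the total are already in the file, and the Protocol gives no control value or SD for a 0-8 score.

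The cost is some extra scoring from the recordings, a few more lines of reporting, and a broader, less specific primary claim. The sample-size calculation need not change, because the primary score itself does not.

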## Funding

This study is not sponsored.

The conduction of the study does not add additional costs for the participating institutions.

The interventional videos are freely available on several websites and are not covered by copyright or royalties. Phone calls are made from a telephone within the IRCCS Ospedale San Matteo at negligible costs.

The software used for phone calls management is also freely downloadable from the internet.

Since the intervention under study is an educational video and not a drug, we will not stipulate any insurance, as the intervention does not constitute a potential harm for patients.

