**Question 4**

|              |                                                              |
|--------------|--------------------------------------------------------------|
| Insufficient | The patient does not recall any symptom at all.              |
| Sufficient   | The patient names at least one of the symptoms listed below. |
| Good         | The patient names at least 1/3 of the symptoms listed below. |
| Very good    | The patient names at least 2/3 of the symptoms listed below. |

| DVT                    | AF                                                   |
|-------------------------------|-------------------------------------------------------------|
| Dyspnoea/Shortness of breath  | Palpitations/tachycardia                                    |
| Chest pain                    | Bleeding (iatrogenic)                                       |
| Sense of imminent death       | Mental confusion                                            |
| Tachycardia/palpitations      | Syncope/Loss of consciousness                               |
| Syncope/Loss of consciousness | Visual disturbances/sudden drop in visus                    |
| Bleeding (iatrogenic)         | Vertigo/dizziness/postural instability                      |
|                               | Speech disturbances                                         |
|                               | Sensory disorders (altered sensation of a part of the body) |
|                               | Motor disorders (altered strength of a part of the body)    |

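### The two added safety outcomes can show harm from poorer anticoagulant adherence, but not the bleeding that better adherence could bring, and all-cause death is not recorded

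*Protocol*

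**What the plan says.** The Outcomes section states: "In this second version of the protocol, we added two safety outcomes". It then names them. "The first is patient adherence to anticoagulation prescribed at hospital discharge"; this is to be read off the recording of the interview held within 48 hours of discharge. "The second outcome is incidence of the main complication (stroke/pulmonary embolism) at a median follow up"; for this, "Incidence of complications at median follow up will be assessed via a second telephone contact with recruited participants (patients or caregiver"), with at most five attempts before the participant counts as lost. The reason given is: "This amendment is felt necessary due to relatively frequent patient-reported non-adherence to anticoagulants observed during telephone interviews".

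The main complication has a fixed meaning. The scoring key for Question 3a (Supplementary Data 4) makes it stroke for AF and pulmonary embolism for DVT, and the Interventions section describes both as the result of a clot that has moved.

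Bleeding appears only in the scoring key for Question 4, which asks: "What symptoms would worry you enough to return to the Emergency Department?" The entry "Bleeding (iatrogenic") stands in both the DVT and the AF symptom list. It is something a patient should know, not an event to be counted.

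Nothing else in the document collects it. Statistical methods says that the SAP holds no detail on adverse event rates because this does not suit the study, and the appended CONSORT checklist marks Harms as not applicable.

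**The concern.** Background and rationale calls comprehension the main predictor of compliance with discharge instructions, and the amendment is prompted by patients not taking their anticoagulants. If the video works as argued, more patients in that arm take the drug. Adherence then rises and clot-derived events should, if anything, fall, so both safety outcomes move in the video's favour. The expected cost of the same change is bleeding on treatment, and neither outcome is designed to show it. The trial would score whether patients know that treatment can make them bleed without counting whether they bled.

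The gap on death is a separate weakness. The second call uses the contact details given at recruitment. If a participant has died and nobody answers, the five-attempt rule turns a death into a missing value. The safety result then loses exactly the participants who matter most to it.

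**Working it through.** **Which events the named outcomes can register**

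| Event | Named outcome? | Where it would appear |
|---|---|---|
| Not taking the anticoagulant | Yes | First interview recording, within 48 hours |
| Stroke (AF) or PE (DVT) | Yes | Second call |
| Haemorrhagic stroke | Possibly; stroke type is not specified | Second call, pooled with clot-derived events |
| Other bleeding | No | Nowhere stated |
| Death from stroke or PE, reported by a caregiver | Yes, as stroke or PE | Second call |
| Death from another cause | No | Nowhere stated |
| Any death, nobody reached in five attempts | No | Lost to follow-up |

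A participant who takes the drug and is admitted with a bleed two weeks later would be adherent from the first interview and free of the main complication at the second call.

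**What the trial could say about bleeding**

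The documents give no figure for any safety outcome, so there is none to reproduce. The denominators come from Sample size: 64 / 0.90 = 71.1, rounded up to 72 enrolled per arm. This matches the plan and leaves about 64 after the expected 10% loss.

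With zero events among m participants, the exact two-sided 95% upper bound is 1 − 0.025^(1/m):

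- m = 72 (everyone reached): 1 − 0.025^(1/72) = 4.99%
- m = 64 (after 10% loss): 1 − 0.025^(1/64) = 5.60%

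Supplementary Data 5 shows 69 and 68 participants reached at the first interview, which gives 1 − 0.025^(1/69) = 5.2% and 1 − 0.025^(1/68) = 5.3%. Reach at the second call is not given.

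The bound is wider among those prescribed an anticoagulant, because Question 3b provides for patients sent home with no new medication. That share is not given. If it were 75% or 50% of 64 (assumed), m would be 48 or 32, and the bounds would be 1 − 0.025^(1/48) = 7.4% and 1 − 0.025^(1/32) = 10.9%.

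**Whether bleeding could be tested**

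The documents give no bleeding rate, so control rates of 1% to 5% are assumed, with a doubling under video. With p̄ the mean of the two rates and n per arm, power = Φ{[√n·|p₂ − p₁| − 1.96·√(2p̄(1 − p̄))] / √(p₁(1 − p₁) + p₂(1 − p₂))}. For 5% against 10% at n = 72 this is Φ[(0.424 − 1.96 × 0.3725) / 0.3708] = Φ(−0.825) = 0.205. The last column is 1 − (1 − p₁)^72.

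| Assumed rates | Power at 72 per arm | n per arm for 80% power | Chance of at least one bleed in 72 controls |
|---|---|---|---|
| 1% vs 2% | 7% | 2319 | 52% |
| 2% vs 4% | 10% | 1141 | 77% |
| 3% vs 6% | 14% | 749 | 89% |
| 5% vs 10% | 21% | 435 | 97.5% |

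A test would be uninformative. A count would probably not be empty, and it is worth reporting with its interval.

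**The case against.** The strongest reply is that this asks for an extra outcome in a trial of a short educational video. The aim is superiority on comprehension, and the two added outcomes answer the problem that prompted them, which was non-adherence. Listing bleeding as a symptom to recall is no promise to count it, so the document does not contradict itself. At this sample size bleeding counts would not alter the comprehension conclusion. All of that stands, and it limits the weight of the point. It does not remove it: the outcomes are labelled as safety outcomes, and the omitted event lies on the pathway that the protocol relies on.

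Several stronger readings are tempting, but the documents do not support them:

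- **That the safety outcomes can only favour the video.** Adherence could fall or stroke/PE could rise in the video arm, and both would be seen. What goes unseen is the harm of better adherence.
- **That every bleed is missed.** Stroke is not limited to ischaemic stroke, so a haemorrhagic one might be counted, though it would then be mixed with clot-derived events. The script of the second call is not shown, so the evidence is the stated outcome list, not the call's full content.
- **That the second call would record a patient who bled as adherent.** Adherence comes from the first interview only.
- **That the protocol claims safety and leaves the claim untested.** The statement that "the intervention does not constitute a potential harm for patients" stands under Funding and explains why no insurance is taken out. Nothing says the trial will declare the video safe.
- **That fatal stroke or PE falls outside the outcomes.** It falls within the second one if somebody reports it. The gap concerns other causes of death and deaths where nobody answers.

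**Conclusion.** The point holds in this limited form and should be acted on. The safety outcomes can detect harm from poorer adherence, but not the main expected harm of better adherence, and all-cause death is not recorded. The unseen SAP cannot be presumed to fill the gap: outcomes and data collection are set in the protocol, which itself says that adverse event rates are not in the SAP.

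The size is modest. With zero bleeds per arm, a rate of up to about 5.0% (72 reached) or 5.6% (64 reached) could not be excluded, and a higher one among those prescribed an anticoagulant. Power for a doubling is 7% to 21% under the assumed control rates, so only descriptive reporting is justified.

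The conclusion assumes that the second call collects no more than the Outcomes section names, and that the iatrogenic bleeding in the symptom lists is bleeding on the prescribed anticoagulant, which the protocol implies but does not spell out. The primary comprehension analysis is unaffected.

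**What to change.** 1. At the second call already planned, ask every participant or caregiver in both arms the same fixed items: stroke, pulmonary embolism, bleeding that led to an ED visit, hospital admission or transfusion, and death.
2. In Outcomes, list bleeding (so defined) and death from any cause as safety outcomes beside stroke/PE.
3. Report counts by arm with exact 95% confidence intervals, giving the number reached and, for bleeding, the number prescribed an anticoagulant. Do no hypothesis test, and limit the conclusion to that precision.
4. Results are already appended to the document. If the second calls are complete, state in the report that bleeding and death were not collected, and make no general safety claim.

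The cost is two more items in a call already planned and two more table rows, with no change to the sample size. The small downside is that self-reported bleeding is less specific, which the ED visit, admission or transfusion criterion limits.
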